### Strategies to improve adherence to interventions {11c}

ResNs allocated to each site received training regarding Good Clinical Practice (GCP), the study protocol (including subsequent amendments), intervention, recruitment strategies, data collection using an electronic database, and inspection of the sacrum surgical site including how to take photographs (in terms of consistent angle, lighting, and distance where possible) and edit photographs prior to commencement in the role. A manual detailing the standard operating procedures (SOP) for the trial (including subsequent updates) is available to all members of the research team for top-up training to ensure ongoing protocol adherence and consistency. The information provided ensures all participants receive identical verbal and written information and instructions regarding the study. In addition, ResNs have received education from the dressing manufacturer representatives.

Audits of 10% of photographs have been taken to evaluate the quality of photographs (e.g. lighting, angle, distance) and photo modification to conceal dressing markings. Detailed instructions and images have been added to the SOP to provide continued support to ResNs and training new staff.

Regular assessment of treatment fidelity by the clinical trial coordinator (CTC) focuses on data integrity, the trial dressing and its application, photography, and image editing. Fleiss Kappa analysis will estimate inter-rater reliability between blinded outcome assessors. A score of ≥08 will be considered acceptable.

### Relevant concomitant care permitted or prohibited during the trial {11d}

Routine care according to hospital procedures and informed by state governance and international standards [1, 18] continues throughout the trial for all participants.

### Provisions for post-trial care {30}

Routine care according to hospital procedures informed by state governance and international standards [1, 18] is provided within the public health service in Queensland, Australia.

### Outcomes {12}

#### Outcome measure primary outcome

Cumulative incidence ratio will be calculated as a proportion of the difference between the number of sacral HAPI between the intervention and control groups (i.e. representing relative benefit). The difference in the risk of developing sacral HAPI within 14 days will be used to test the difference between the prophylactic silicone foam dressing and routine care.

#### Secondary outcomes

Time to onset of sacral HAPI in days up to 14 daysSacral HAPI incidence rates per 1000 bed daysSeverity of sacral HAPI up to 14 days, i.e. depth of tissue damage assessed using an internationally and nationally recognised classification system [1, 18]. This classification is based on the depth of skin and tissue damage, from non-blanchable erythema (stage 1) to full thickness tissue loss (stage 4) and unstageable damage and suspected deep tissue injuryCost-effectiveness (an additional 14 days, up to 28 days): via an economic evaluation to compare the healthcare costs of prevention (using the prophylactic sacral dressings in addition to routine care compared to routine care alone) and benefits of prevention in terms of any difference in either incidence or treatment costs of sacral HAPIProcess (implementation) evaluation to determine intervention fidelity will allow a better understanding of the hospital contexts in which the trial was implemented. A process evaluation will identify contextual factors and co-interventions related to hospital procedures or individual clinical practice that may operate concurrently with the intervention. Fidelity will assess whether the delivery of the intervention to participants as outlined in the SOP and training processes is consistent (via quantitative monitoring and assessment methods) and explored (via qualitative methods)

### Participant timeline {13}

The participant timeline is shown in Table 1.

**Table 1 Tab1:** Participant timeline based on the SPIRIT statement [19]

	Study period						
	Enrolment and allocation	Baseline data collection	Daily data collection (post-allocation)		Study exit	Evaluation	Trial close-out
Time point			***Up to 14 days*** *Prevention*	***Up to 28 days***^e^ *Treatment*			
**Enrolment** (within 36 h of hospital admission)							
**Eligibility screen**	X						
**Informed consent**	X						
**Allocation** (randomisation)	X						
**Baseline data collection**							
Hospital information		X					
Participant demographics		X					
Participant health data		X					
PI risk assessment		X					
Photography of the sacrum		X					
Application of dressing (intervention only)		X					
**Intervention**							
Routine care only			X				
Routine care + prophylactic dressing			X				
**Outcome variables**							
Skin assessment^a^			X				
De-identified photograph of the sacrum and photo editing			X				
Dressing change/reason^b^			X				
HAPI			X				
Other complications^c^			X				
**Economic evaluation**							
Hospital length of stay^d^					X		
Dressing used for HAPI			X				
Staff time to apply, remove, and change dressing for prevention (subsample)			X				
Resources used to treat any local adverse effects of dressings for prevention			X				
Other resources used to prevent HAPI			X				
Resources (including dressings) used to treat HAPI				X			
**Process evaluation** [16]							
Context			X	X		X	
Fidelity			X	X		X	
Dose delivered			X	X		X	
Dose received (exposure)			X	X		X	
Recruitment	X	X				X	
Reach	X	X				X	
**Discharge, death, or withdrawal**					X		
***Reports to HREC, funding body, site visits, DSMB meetings***							X^f^

*HAPI* hospital-acquired pressure injury, *HREC* Human Research Ethics Committee, *DSMB* Data Safety Monitoring Board

^a^Participants’ demographic and clinical data, e.g. gender, diagnosis, reason/type of admission, mobility status, body mass index (BMI), nutritional deficiencies, the type of and number of comorbidities, smoking status, PI risk, existing PI (other than sacral) and its treatment/management, previous history of PI, number of days enrolled in the trial, and hospital length of stay, will be recorded in a separate electronic case report form

^b^Dressing change/reason = may include skin itchiness/irritation dressing soiled, rolled-up, saturated, in situ for more than several days or as indicated by clinical practice (as per manufacturer recommendations), or other device deficiency

^c^Other complications = allergic reaction, persistent faecal incontinence, unable to be moved

^d^Hospital length of stay recorded for all trial participants

^e^Only relevant for participants who develop HAPI within the 14-day trial will be followed up until day 28

^f^Reports to HREC, funding body, site visits, and DSMB meetings are also completed at multiple, specific time points during the trial (e.g. annual HREC reports)

### Sample size {14}

The sample size is based on the effect size reported in published research [2]. HAPI cumulative incidence in similar settings ranged from 4 to 13% in The Border Trial [8]. We based calculations on an expected effect of intervention on the primary outcome, calculated using a cumulative incidence ratio of 0.5 (0.46 in our pilot trial) [13], between groups. This assumed a cumulative incidence of 5% in the intervention group compared to 10% in the control group. To obtain 90% power with a two-sided *α* level of 0.05, a total 578 patients per group are required. To allow for attrition, a further 10% will be recruited with a total sample of 1320 (*n* = 220 per group/site).

### Recruitment {15}

Our target sample is 1320 participants (i.e. 220 per group/site) which also accounts for an anticipated 10% lost to follow-up. Originally, the recruitment phase was to be completed in about 3.5 years, dependent upon seasonal fluctuations, hospital bed closures, and holiday periods. However, the COVID-19 pandemic has delayed the trial considerably, hence its extension to December 2023.

A screening tool reflecting inclusion and exclusion criteria to identify potential participants was specifically developed based on our previous research in this area [13]. Based on screening criteria, the ResN approaches the potential participant and invites them to participate via the informed consent process.

## Assignment of interventions: allocation

### Sequence generation {16a}

Following eligibility assessment and consent, participants are randomised to either the dressing group or the routine care only group using a 1:1 ratio, permuted block sizes of four, six, and eight, stratified by hospital and division (i.e. medical or surgical).

### Concealment mechanism {16b}

Randomisation is computer-generated via a secure website and can be accessed via a mobile electronic device.

### Implementation {16c}

ResNs at each site log in to a central randomisation service via a secure website, independent of the trial via a mobile electronic device.

## Assignment of interventions: blinding

### Who will be blinded {17a}

While one investigator ([name]), ResNs, the clinical trial coordinator (CTC), nursing staff, and participants are aware of group allocation, the outcome assessors and research team members (including the trial statistician) are blinded to group allocation and analysis. Given the intervention, it is not feasible for patients, healthcare professionals, and ResN to be blinded to group allocation.

On the day of recruitment, ResNs at each site take high-resolution, de-identified digital photographs (including study number, date, and time) of each participant’s sacrum. All photographs are edited using photographic software to “blur” surrounding skin to ensure atraumatic skin markings from the dressing are not visible, before the photographs are forwarded to a blinded, independent outcome assessor.

The outcome assessors have expertise in identifying PIs and evaluate photographs according to the established international classification system [1]. The outcome assessor allocated on the day makes and discloses their assessment back to the ResNs on the same day as the photograph is taken and provided to the assessor.

### Procedure for unblinding if needed {17b}

There is no requirement for emergency unblinding procedures (refer to the “Who will be blinded {17a}” section).

## Data collection and management

### Plans for assessment and collection of outcomes {18a}

After screening, consent, and randomisation, data are collected directly from the participant or their proxy, and their health record at baseline and then daily for up to 14 days until the trial endpoint (i.e. development of a new sacral HAPI, discharge, or death—whichever occurs first). Participants who develop a HAPI in either arm exit the prevention trial and are followed up for up to 14 days (until discharge or death—whichever comes first) for a total of up to 28 days, to provide data on PI treatment to support the economic evaluation.

Each recruited participant’s hospital information (date of birth, unique record number) is recorded in an eCRF available only to investigator [name], the CTC, and site ResNs to ensure participant confidentiality. Participants’ demographic and health data including gender, diagnosis or surgery, reason for admission, mobility status, body mass index, nutritional deficiencies, the type of and number of comorbidities (such as cardiovascular disease, diabetes, cognitive impairment, and malnutrition on admission), current smoking status, PI risk, existing PI (other than sacral) and its treatment/management, previous history of PI, number of days enrolled in the trial, and HLOS (documented at discharge for all participants) is recorded in a separate eCRF (electronic clinical research form). A photograph is taken of the patient's sacral skin and sent to the blinded outcome assessor to confirm its diagnosis. A trained CTC monitors recruitment and data collection across all sites and monthly reports are presented to the chief and associate investigators.

As part of the process evaluation, where a patient is unable to provide information for self-report data (e.g. Patient Participation in Pressure Injury Prevention Scale, assessment of satisfaction and comfort), the ResN documents the reason [16]. These data are considered “missing” data for the purpose of analyses, but the reason and proportion of participants who do not have these data due to cognitive impairment, for example, will be reported in reports/publications. For other data that requires participant self-report (e.g. in the instance where weight or height is not documented), the ResN elicits this information from the participant’s proxy if possible or attempts to collect this data in accordance with the protocol and SOP manual (e.g. patient’s medical record, Demi Span, using chair scales on the ward where possible).

Data on resource utilisation associated with prevention are collected including the number of dressings used; personnel time to apply, remove, and change dressings; and any treatment required for any local adverse effects from the dressings. To enable an extended cost-benefit analysis, resources used to treat sacral HAPI are also recorded for those patients that develop a sacral PI during the trial. HLOS is recorded for all trial participants on discharge from hospital.

Digital photography is a novel and practical solution to address blinding. Using study-specific and password-protected iPads, research nurses at each site take high-resolution, de-identified digital photographs of every participant’s sacrum at baseline and each subsequent day they are enrolled in the trial. Photographs are edited using Adobe photo editing software to “blur” surrounding skin to conceal atraumatic skin markings for participants in the intervention group or other markings that may indicate the participant is in the control group (e.g. clothing or bedsheets). Except for the baseline photograph, all modified photos are uploaded into a secure data collection platform and forwarded to a blinded outcome assessor on the same day they are taken. Where a stage 1 (i.e. non-balanceable erythema) is suspected, the patient is be repositioned where possible, the site reassessed after 30 min, and the photograph taken (35). For each photograph, the ResN notifies the blinded outcome assessor as to whether the skin is blanching or non-blanching. The patient exits the clinical study if it is determined they have developed a sacral HAPI which is reported to clinical staff. If the clinical staff caring for the patient diagnose a stage 1 HAPI (even if the blinded assessor did not), the patient is still exited from the study. However, this decision is not disclosed to and therefore does not influence the assessment of the blinded outcome assessor. If the patient has a sacral HAPI, they are included in the estimation of PI treatment costs.

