**Methods:**

This is a multicentre, pragmatic, parallel group, randomised controlled trial. A sample size of 1320 was calculated to have >90% power to detect a 5% difference in the primary outcome at an alpha of 0.05. Adult patients admitted to participating medical-surgical wards are screened for eligibility: ≥18 years, admitted to hospital within the previous 36 h, expected length of stay of ≥24 h, and assessed high risk for hospital-acquired pressure injury. Consenting participants are randomly allocated to either prophylactic silicone foam dressing intervention or usual care without any dressing as the control group via a web-based randomisation service independent of the trial. Patients are enrolled across three Australian hospitals. The primary outcome is the cumulative incidence of patients who develop a sacral pressure injury. Secondary outcomes include the time to sacral pressure injury, incidence of severity (stage) of sacral pressure injury, cost-effectiveness of dressings, and process evaluation. Participant outcomes are assessed daily for up to 14 days by blinded independent outcome assessors using de-identified, digitally modified sacral photographs. Those who develop a sacral pressure injury are followed for an additional 14 days to estimate costs of pressure injury treatment. Analysis of clinical outcomes will be based on intention-to-treat, per-protocol, and sensitivity analyses.

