### Intervention description {11a}

#### Intervention: routine care plus dressing

If allocated to the intervention group, participants have a prophylactic sacral dressing applied by a trained research nurse (ResN), following the manufacturer’s instructions. The trial dressing is the Mepilex® Border Sacrum, a foam border silicon dressing available in two sizes to accommodate physical differences of participants. The dressing manufacturer recommends the dressing be changed when the edge begins to roll and/or loses adhesion or becomes soiled. Dressings will also be changed if saturation occurs, if staff accidentally remove the dressing, or if the dressing becomes dislodged.

The ResN takes a baseline photograph of the participant’s sacrum and then applies a silicone foam border dressing (Mepilex®). The dressing and sacral skin are visually inspected every day for up to 14 days. The frequency of dressing replacements (with reason, including device deficiencies) will be documented. Participants in the intervention group will continue to receive routine care, as per hospital procedures informed by national standards and international practice guidelines [1, 18].

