## Statistical methods

### Statistical methods for primary and secondary outcomes {20a}

The patient is the unit of measurement. The primary outcome, development of a new sacral HAPI, is dichotomous. The main analysis will be based on comparisons of the cumulative incidence of pressure injuries in the two groups. Relative risk (RR) of HAPI for the intervention group compared to the control group will be computed and reported along with 95% confidence intervals and *P* values.

We anticipate that prognostic imbalance of known (e.g. age, BMI, number of comorbidities) and unknown prognostic factors is unlikely between the groups due to central randomisation and treatment concealment. However, if we find any differences, we will conduct adjusted analyses using multiple regression models. We do not expect effect sizes to vary between hospitals, but centre-to-centre variability will be assessed, and cluster-adjusted analysis will be carried out as a form of sensitivity analysis if required. Patients’ declining to participate in the trial are given the opportunity to consent to some non-identifiable data being collected (i.e. admission type, age, sex, and PI risk score). These data will enable us to compare some characteristics of eligible and consenting patients (i.e. participants) versus patients who are eligible but not consenting (i.e. non-participants).

For the secondary endpoints, “time to HAPI” will be analysed using the Kaplan-Meier curve and log rank tests. Hazard ratios along with 95% confidence intervals will be reported. Additional Cox regression models will be used to detect the influence of prognostic factors. As for the “stage of HAPI”, a chi-square test will evaluate if the intervention group differs from the control patients. All data will be entered directly into a web-based data collection tool (REDCap) and then exported into SPSS (V 24). Prior to analysis, a rigorous process of data cleaning to check outlying figures, missing, and implausible data against source data will be undertaken. Sample attrition will be managed via intention-to-treat analysis to ensure an unbiased comparison of the groups by randomisation. An expert biostatistician will lead all analyses.

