## Discussion

This protocol outlines the design of this pragmatic RCT to examine the effect of prophylactic sacral dressings on the cumulative incidence of PI in hospitalised adults. Our trial has several strengths. We are using an appropriately powered, robust multicentre pragmatic RCT design that is the largest trial of its kinds in this area. We are conducting an economic evaluation alongside the trial, and a process evaluation to ensure any difference in outcomes between the groups can be attributable to the intervention or contextual issues. With so few economic studies in this area, this parallel cost-effectiveness analysis will provide valuable health economic information to guide decision-making of health service managers to better balance quality patient care with economic efficiencies [21]. Digital photography and photo editing software are being used, which enables blinded, independent outcome assessors to assess the sacral skin for PI remotely, thereby reducing their ability to identify group allocation. This method represents a significant and innovative approach to clinical research. Finally, this multicentre RCT is independent of industry funding and therefore minimises potential for a conflict of interest and bias.

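### Stage 1 is only partly blinded in the primary outcome: the allocation-aware research nurse tells the assessor whether the skin blanches

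*Protocol article*

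**What the plan says.** Protocol article, section by section:

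- **Abstract, Methods.** Outcomes are assessed daily "by blinded independent outcome assessors using de-identified, digitally modified sacral photographs".
- **Who will be blinded {17a}.** "ResNs, the clinical trial coordinator (CTC), nursing staff, and participants are aware of group allocation"; the section adds that "it is not feasible for patients, healthcare professionals, and ResN to be blinded to group allocation". The assessor classifies the injury.
- **Intervention description {11a}.** "The ResN takes a baseline photograph of the participant’s sacrum and then applies a silicone foam border dressing".
- **Plans for assessment and collection of outcomes {18a}.** "For each photograph, the ResN notifies the blinded outcome assessor as to whether the skin is blanching or non-blanching". Where stage 1 is suspected, the patient is repositioned if possible and the site is reassessed after 30 minutes before the photograph is taken. A stage 1 diagnosis by clinical staff is kept from the assessor.
- **Secondary outcomes {12}.** The severity scale runs "from non-blanchable erythema (stage 1) to full thickness tissue loss (stage 4", with unstageable damage and suspected deep tissue injury in addition.
- **Statistical methods {20a}.** "The primary outcome, development of a new sacral HAPI, is dichotomous". No minimum stage is set, and {11b} and {18a} treat stage 1 as a pressure injury that ends participation in the prevention trial.
- **Discussion.** Photography and editing software are credited with a design that "enables blinded, independent outcome assessors to assess the sacral skin for PI remotely".

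**The concern.** Blanching is found by a test at the bedside, and under {18a} the assessor receives the result from the nurse. For red skin with no break, the photograph can show the redness, but the nurse's report settles whether it is stage 1 or no event. The nurse knows the arm and, in the dressing arm, applied the dressing.

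A tendency to call blanching differently by arm would therefore pass straight into the primary outcome, in a trial whose photographic method is meant to guard against exactly that. Because any stage counts as an event, the exposure grows with the share of events that are stage 1.

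**Working it through.** **1. Does any stated safeguard cover this route?**

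| Safeguard | Where | What it covers | Covers the blanching report? |
|---|---|---|---|
| Blurring of surrounding skin | {17a}, {18a} | Visible signs of the arm | No |
| Withholding the clinical staff's diagnosis | {11b}, {18a} | A different bedside opinion | No |
| Reassessment after 30 minutes | {18a} | Consistency of the bedside call | Structures it, does not blind it |
| Fleiss kappa | {11c} | Agreement between assessors | No: assessors given the same report can agree on a biased one |
| Chi-square test on stage | {20a} | Severity by arm | Shows stage counts, not where a bias came from |

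**2. The plan's own figure.** Sample size {14} uses 10% v 5%, two-sided alpha 0.05 and 90% power. The unpooled formula gives (1.960 + 1.282)² × (0.10 × 0.90 + 0.05 × 0.95) / 0.05² = 577.9, so 578 per group, as stated. With 1320 recruited and 10% lost, 1320 × 0.9 / 2 = 594 per arm remain. These figures are not in dispute.

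**3. What differential calling could do.** This is an illustration. From the document: 10% risk (applied to both arms, so no true effect) and 594 per arm. Assumed, with no source in the document: the share *s* of events that are stage 1, and the fraction *m* of stage 1 events in the dressing arm that are lastingly called blanching.

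Observed dressing risk = 0.10 × (1 − *s·m*), so the apparent risk ratio is 1 − *s·m*. The probability of a significant result favouring the dressing is Φ[(*d* − 1.960·SE₀)/SE₁], where *d* is the risk difference, SE₀ the pooled standard error and SE₁ the unpooled one.

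Worked cell, *s* = 0.7 and *m* = 0.2: the observed risk is 0.086, *d* = 0.014, and SE₀ and SE₁ are both about 0.01685. (0.014 − 0.0330)/0.01685 = −1.13, and Φ(−1.13) = 0.129.

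| Stage 1 share | *m* = 10% | *m* = 20% | *m* = 30% |
|---|---|---|---|
| 50% | RR 0.95; 4.8% | RR 0.90; 8.5% | RR 0.85; 14.3% |
| 70% | RR 0.93; 6.0% | RR 0.86; 12.9% | RR 0.79; 24.4% |
| 90% | RR 0.91; 7.6% | RR 0.82; 18.9% | RR 0.73; 38.0% |

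The nominal value is 2.5%. Over-calling in the dressing arm would move the ratio the other way.

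**4. Could agreement in direction at stage 2 or worse serve as a pass/fail check?** Binomial counts, 594 per arm:

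- No true effect, 30% of events at stage 2 or worse: 594 × 0.03 = 17.8 expected per arm. The dressing arm has fewer events about 47% of the time by chance.
- Planned effect, same share: 17.8 v 8.9 expected. The comparison ties or reverses about 5% of the time.
- Planned effect, 10% of events at stage 2 or worse: 5.9 v 3.0 expected. It ties or reverses about 20% of the time.

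Such a rule would often pass a biased result and sometimes fail a true one.

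**The case against.** A reader might infer that the nurse decides stage 1, or that the blinded assessment is an unblinded call passed through a blinded reader. The document does not support that. The assessor sees whether redness is present and assigns the stage, and a non-blanching report on skin that looks normal need not produce an event. The nurse supplies one input, although it is the one that separates stage 1 from ordinary redness.

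The article is also open about this. It states that nurses are unblinded and that they report blanching, and its Discussion claims a reduced ability to identify the arm, not complete protection. Some reliance on a person at the bedside may be unavoidable. The operating manual is not shown, so how blanching is tested cannot be judged.

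The illustration is easy to over-read as well. Both inputs are assumed, only one direction is modelled, and each miscall is treated as lasting. Assessment is daily for up to 14 days, so a persisting lesion may be called correctly later or progress to a stage that needs no blanching report. A lasting loss generally needs repeated miscalls, unless the patient leaves first.

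Finally, severity by stage is already compared between arms, and a sensitivity analysis by stage may sit in an analysis plan that is not shown. Its absence from the article is not the fault raised here.

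All of this stands, and it limits the size and wording of the point. It does not remove the route from an allocation-aware nurse to the stage 1 classification, which no stated safeguard covers.

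**Conclusion.** The point holds in limited form: stage 1 ascertainment, and so that component of the primary outcome, is only partly blinded. Stage 2 or worse is not affected through this route.

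The document gives neither the stage 1 share nor any evidence of differential calling, so no actual bias can be claimed or sized. The ranges in the table (RR 0.95 to 0.73; 5% to 38% against 2.5%) show what modest, lasting under-calling in one arm could do. They are likely upper-side figures for a given rate of single miscalls, because daily reassessment would dilute them. The practical fault is that, as described, such a bias would go undetected.

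**What to change.** Keep the current primary outcome definition and make the influence of the nurse's report visible:

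1. From now on, the assessor records a photo-only reading (no lesion; erythema; stage 2 or worse, including unstageable and suspected deep tissue injury) before the blanching field is shown, and then the final stage. For participants already enrolled, a blinded photo-only re-read is optional; Data management {19} says photographs are kept.
2. Pre-specify the between-arm risk ratio with 95% confidence interval for stage 2 or worse, including unstageable and suspected deep tissue injury, as a supportive sensitivity analysis.
3. Compare by arm the nurse's blanching calls among photographs read as erythema.
4. Describe stage 1 ascertainment as partly blinded in the protocol and the report.

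Do not make the trial's conclusion depend on agreement in direction, for the reason in step 4 of the working.

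The cost is a short extra reading step on each same-day photograph, introduced mid-trial, with incomplete data for earlier participants. Events at stage 2 or worse will be few, so the checks are imprecise and supportive only. A photo-only reading of erythema includes blanching redness, which is not a pressure injury, and possibly dressing marks, so any arm difference in it needs cautious reading.

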### Criteria for discontinuing or modifying allocated interventions {11b}

#### Intervention

Where there is evidence of skin irritation and/or participant-reported discomfort and/or itchiness due to the dressing, the dressing will be removed, the skin reaction reported using standard hospital incident reporting protocols, and the patient exited from the clinical study. Where the patient has developed persistent urinary and/or faecal incontinence, the sacral dressing will be removed, and the patient exited from the clinical study. In our pilot trial, only six participants (5% of the total sample) reported dressing discomfort, due to dressing migration or mild itchiness without any other clinical symptoms of allergic reaction [13].

Note that in either group, diagnosis of a sacral HAPI resulting in the patient exiting the study will be made on a case-by-case basis in consultation with the clinician caring for the patient and/or the team leader. This decision will not influence the assessment of the outcome assessor (i.e. they will not be aware of the decision made by the clinician/team leader). Where there is indecision among the clinical staff caring for the patient regarding the diagnosis of a Stage 1 PI, the assessment by the blinded assessor will be used to determine if the patient should exit the clinical study.

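### A firm ward diagnosis of stage 1 that the blinded assessor does not share ends blinded follow-up, and the protocol does not say how such patients count in the primary outcome

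*Protocol article*

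**What the plan says.** The Abstract (Methods) describes the outcome as blinded: "Participant outcomes are assessed daily for up to 14 days by blinded independent outcome assessors".

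Two sections govern exit for a sacral injury:

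- Section {18a}, on collection of outcomes, covers the discordant case directly. If ward staff "diagnose a stage 1 HAPI (even if the blinded assessor did not), the patient is still exited from the study". It adds that "this decision is not disclosed to and therefore does not influence the assessment of the blinded outcome assessor".
- Section {11b}, on discontinuation, says for either group that "diagnosis of a sacral HAPI resulting in the patient exiting the study will be made on a case-by-case basis in consultation with the clinician". Where staff are undecided about stage 1, "the assessment by the blinded assessor will be used to determine if the patient should exit the clinical study".

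On who knows the allocation, section {17a} says that "nursing staff, and participants are aware of group allocation" and that "it is not feasible for patients, healthcare professionals, and ResN to be blinded to group allocation".

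Section {18a} ties the daily photographs to the days on which the patient is enrolled, and Table 1 puts photography in the prevention phase only. Follow-up after a sacral injury is described in {8} and {18a} as serving the economic evaluation. On costs, {18a} says: "If the patient has a sacral HAPI, they are included in the estimation of PI treatment costs".

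**The concern.** Blinded photographic reading is the main protection against ascertainment bias in a trial where patients and staff can see the dressing. If a ward diagnosis that the assessor does not share stops the photographs, people who know the allocation can end the observation period of the blinded outcome.

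Stage 1 is where this is most likely to matter. It is non-blanchable redness, and {11b} itself expects staff to be unsure about it at times. If staff call it more readily in one arm, blinded follow-up is shortened more in that arm. The article does not say how such a patient enters the primary analysis, and either answer has a cost:

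- If the ward call counts as an event, the primary outcome is partly unblinded.
- If it does not, the patient is a non-event whose later photographs were never taken.

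**Working it through.** **Does blinded observation stop?** Setting the sections side by side: exit follows a firm ward stage 1 call despite a negative blinded reading ({18a}); the ward knows the allocation ({17a}); photographs run only while the patient is enrolled ({18a}, Table 1); later follow-up is for treatment and costs ({8}, {18a}). So no blinded reading is described after such an exit.

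**Is it caught as missing data?** Section {20c} defines loss to follow-up as having no outcome assessment at all. A discordant exit with one or more photographs falls outside that definition, so the best-case and worst-case analyses are not clearly triggered. In the time-to-event analyses of {20a}, censoring at a suspected injury would be informative.

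**The plan's own sample size.** Section {14} gives 10% versus 5%, 90% power, two-sided alpha 0.05, and 578 per group. With unpooled variance, n = (1.960 + 1.2816)² × (0.10×0.90 + 0.05×0.95) / 0.05² = 577.9, so 578. It reproduces, and the sample size is not at issue.

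**Illustration.** The documents give no rate of ward-only exits, so the following are assumptions:

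- n = 594 per arm, from 1320/2 = 660 less the planned 10%.
- Half of ward-only exits would later have been confirmed by a blinded reading.
- These patients are counted as non-events.

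Observed risk = true risk − exit share × 0.5.

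Power = Φ[(difference − 1.96·SE₀)/SE₁], where SE₀ = √(2p̄(1−p̄)/n) and SE₁ = √((p₁(1−p₁) + p₂(1−p₂))/n).

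| Exits, control / dressing | Observed risks | RR | Power |
|---|---|---|---|
| none | 10.0% / 5.0% | 0.50 | Φ[(0.050 − 1.96×0.01528)/0.01521] = 90.6% |
| 1% / 0.4% | 9.5% / 4.8% | 0.505 | Φ[(0.047 − 1.96×0.01495)/0.01489] = 88.3% |
| 5% / 2% | 7.5% / 4.0% | 0.533 | Φ[(0.035 − 1.96×0.01351)/0.01347] = 73.7% |

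The 5%/2% row removes 2.5/10 = 25% of control events and 1/5 = 20% of dressing events. Most of its power loss comes from fewer events. With control at 7.5% and RR held at 0.50 (dressing 3.75%), power would already be Φ[(0.0375 − 1.96×0.01337)/0.01333] = 80.2%.

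**With no true effect (10% in both arms):**

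- 1% / 0.4% exits: 9.8/9.5 = RR 1.03.
- 5% / 2% exits: 9.0/7.5 = RR 1.20.
- 2% / 5% exits (reversed): 7.5/9.0 = RR 0.83.

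**The case against.** The strongest reply is that the gap is narrow and can be handled. Section {11b} sends undecided stage 1 cases to the blinded assessor, so only a firm ward call against a negative blinded reading remains. The explicit override in {18a} is confined to stage 1. Where stage 1 is suspected, {18a} also asks for repositioning where possible and reassessment after 30 minutes before the photograph, and the assessor is told the blanching status. All of this stands. It reduces the number of discordant exits without removing them.

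The rule that the assessor is not told of the ward decision is a real protection, but only for photographs already taken.

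A reader might infer that unblinded staff decide who becomes a primary event. The text does not support that: they can end observation early for discordant stage 1 calls, but they cannot create or undo a blinded reading. A reader might also infer that the bias is beyond any later analysis. That goes too far. Discordant exits can be counted by arm and bounded as events or non-events, and an analysis plan that is not shown may say how they are counted. Still, no analysis plan can recover readings that were never made.

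A reader might further infer that the economic evaluation uses two different case definitions. The article does not state this. It does not say whether a ward-only diagnosis qualifies for treatment costs, so this is an ambiguity.

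**Conclusion.** The point holds for discordant stage 1 cases. Staff who know the allocation can truncate blinded ascertainment of the primary outcome, the article does not say which diagnosis counts, and these patients fall outside its definition of loss to follow-up.

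The size runs from negligible to serious depending on a discordance rate that the documents do not give. The direction is also unknown. Equal proportional loss of events in both arms would leave the RR unchanged and cost only power. The exit shares and the one-half confirmation rate are assumptions.

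This is a should-fix. It is an avoidable route to bias in the primary outcome, but its frequency is unknown, a partial safeguard exists, and its effect can be bounded.

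**What to change.** 1. State that the blinded reading alone defines the primary event.
2. After a ward-only stage 1 diagnosis, continue daily photographs and blinded reading to day 14, discharge, death or a blinded HAPI, whichever comes first. Clinical care stays with the ward.
3. Report discordant exits by arm.
4. Add sensitivity analyses that count discordant cases as events (blinded or ward diagnosis), and as missing or censored.
5. State one case definition for both effect and treatment cost in the economic evaluation.
6. Reconcile {11b} and {18a} on who determines study exit.

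The cost is wording, some extra photographs and a few added analyses. Research nurses are already on the wards, and patients with a sacral HAPI are followed for up to 14 more days for costs, although whether that covers ward-only cases needs stating. One limit should be acknowledged: later images may show a sacrum already under treatment, so they should be analysed under a treatment-policy approach and will not fully restore the untreated course. For patients who have already exited, only items 3 and 4 can help.
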